### Randomisation

Participants are randomly allocated on a 1:1 basis to the two treatment groups via a central computer-based randomisation system provided by Warwick Clinical Trials Unit (WCTU) independent of the study team. A minimisation algorithm is used to determine participant allocation, using site, gender, age group (<70 years and ≥70 years) and cuff tear size (as assessed by the operating surgeon, ≥3 cm or <3 cm) as factors, with a random element included to provide a 70% chance that the participant will receive the treatment that minimises the imbalance, to ensure unpredictability.

Randomisation will be performed by theatre staff, after the intraoperative findings have been checked (including cuff tear size) and eligibility is confirmed. Staff use an online system in a separate room to maintain blinding, with a 24-hour back-up automated telephone system available.

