#### Group 2: Standard arthroscopic debridement plus insertion of InSpace Balloon (intervention)

Arthroscopic debridement, as described above, with insertion of the InSpace Balloon performed by subspecialty trained shoulder surgeons. The same arthroscopic debridement will be performed as described for the control group. If allocated to the balloon procedure, the company’s recommended surgical technique will be followed for sizing, insertion and deployment of the balloon, as documented in the surgical manual.

For both groups, fidelity will be assessed with an operative record form and arthroscopic photographs taken at the end of debridement and just before balloon inflation, and the number of physiotherapy visits for each participant will be documented in both arms.

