### Statistical analysis plan

All data will be analysed and reported in accordance with the Consolidated Standards of Reporting Trials (CONSORT) guidelines.^62 63^ A detailed statistical analysis plan and a data sharing plan will be agreed with the DMC prior to any formal analyses being conducted.

Baseline data will be summarised to check comparability between treatment arms. Standard statistical summaries (eg, means and SD, dependent on data type) will be presented for the primary outcome measure and all secondary outcome measures.

The primary analysis will investigate differences in the OSS 12 months after surgery between the two treatment groups. It will be conducted on an intention-to-treat basis following the methods, test statistics and boundaries described by Parsons *et al*.^38^ To preserve the integrity of the study, the exact boundaries used for testing are given in the adaptive charter known only to the study team and independent DMC. Briefly, if the study recruits to target, the method set out by Parsons *et al*
38 will be used to calculate the boundaries and if the study stops early, testing will proceed using boundaries calculated by the deletion method for overrunning analysis, described by Whitehead, with clinical inferences following directly from widely used methods for unbiased estimates and confidence intervals in group sequential trials.^64–66^

The primary analysis will be augmented by calculating adjusted estimates of treatment group differences (with 95% CIs) for the OSS using a mixed-effects model. The mixed-effects model will include a random effect for the recruiting centre, and fixed effects for the variables of interest included in the minimisation algorithm, patient age, gender and size of tear. In addition, subject to the observed data, sensitivity analyses such as per-protocol analyses or multiple imputation will also be undertaken. If undertaken, all multiple imputation assumptions will be justified and reported. Estimates of efficacy for the other outcome measures will follow this approach to analysis.

Prespecified subgroup analyses will be undertaken to assess whether there is evidence that the intervention effect differs with respect to:

The size of the rotator cuff tear as measured at the start of surgery, defined as large or massive cuff tear (≥3 cm) or moderate to small (<3 cm).Gender.Age (>70 or <70).

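### The one named analysis bearing on departures from allocation, an optional per-protocol analysis, is open to one-sided selection bias; a complier-average causal effect estimate should be named in its place or ahead of it

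*Protocol article*

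**What the plan says.** The primary analysis of the 12-month Oxford Shoulder Score (OSS) is by intention to treat, supplemented by a mixed-effects model adjusted for the minimisation variables. The Statistical analysis plan section then adds a conditional set of further analyses. It opens "In addition, subject to the observed data, sensitivity analyses" and continues that "sensitivity analyses such as per-protocol analyses or multiple imputation will also be undertaken". Multiple imputation deals with missing data, so per-protocol is the only named method that bears on treatment not received as allocated. The section asks for the imputation assumptions to be justified and reported, and sets no similar condition on per-protocol. It extends the same approach to secondary outcomes: "Estimates of efficacy for the other outcome measures will follow this approach to analysis". Further detail is deferred: "A detailed statistical analysis plan and a data sharing plan will be agreed with the DMC prior to any formal analyses being conducted".

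Three features of the design matter here.
- On timing, the Randomisation section states: "Randomisation will be performed by theatre staff, after the intraoperative findings have been checked (including cuff tear size) and eligibility is confirmed".
- Both arms have the same debridement. The Group 2 section introduces balloon insertion with the condition "If allocated to the balloon procedure".
- On recording, the same section says of both groups that "fidelity will be assessed with an operative record form and arthroscopic photographs taken at the end of debridement and just before balloon inflation". The Blinding section adds that balloon details go into a secure online form.

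**The concern.** The arms differ only in a step that follows randomisation within the same operation. The departure that defines treatment is therefore a balloon allocated but not placed or not deployed. The reverse, a control participant given a balloon, is unlikely, because the Introduction says UK use of the device was restricted to research. Placement is never attempted in controls, so the controls in whom it would have failed cannot be identified and stay in the comparison.

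A per-protocol set that removes failed placements therefore takes a subgroup out of one arm and leaves its counterpart in the other. If that subgroup has a different prognosis, the comparison is biased even when the device does nothing. A per-protocol figure printed beside the intention-to-treat result may be read as the effect of actually having the balloon, and this analysis does not estimate that effect without bias.

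**Working it through.** **The plan's own figure.** Inputs from the Power and sample size section are a difference of 6, SD 12, 90% power and two-sided 5%. Per arm, 2 × (1.960 + 1.282)² × (12/6)² = 84.1, rounded up to 85, so 170 in total. This matches the stated fixed-design size. The stated maximum also follows: 188/0.85 = 221.2, given as 221. The 188 comes from simulations not shown in the article and was not reproduced.

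**Inputs for the bias.** The article gives neither of these, so both are assumptions:
- f, the share of balloon-arm participants whose balloon is not placed: 1% to 10%.
- g, the mean 12-month OSS of placeable shoulders minus that of unplaceable shoulders, both without a balloon effect: −6 to +12 points.

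**Formula.** Let placeable shoulders have mean m, so that unplaceable ones have mean m − g. With no device effect:
- per-protocol balloon-arm mean = m
- control-arm mean = (1 − f)m + f(m − g) = m − fg
- per-protocol difference = **f × g**; intention-to-treat difference = 0.

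**Standard error and type I error.** With 94 per arm (188/2), SE = 12 × √(1/94 + 1/(94(1 − f))). The type I error is for a two-sided 5% normal test centred on the bias. It ignores the sequential design.

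| f | g | Bias (OSS points) | % of 6-point target | SE | Type I error |
|---|---|---|---|---|---|
| any | 0 | 0 | 0 | 1.75–1.80 | 5.00% |
| 1% | 6 | +0.06 | 1 | 1.75 | 5.01% |
| 2% | 6 | +0.12 | 2 | 1.76 | 5.05% |
| 5% | 6 | +0.30 | 5 | 1.77 | 5.33% |
| 5% | 12 | +0.60 | 10 | 1.77 | 6.32% |
| 10% | 12 | +1.20 | 20 | 1.80 | 10.24% |
| 5% | −6 | −0.30 | −5 | 1.77 | 5.33% |
| 10% | −6 | −0.60 | −10 | 1.80 | 6.28% |

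Positive values favour the balloon.

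**Check by simulation.** With f = 5%, g = 6, no device effect and 20,000 trials of 94 per arm, the mean per-protocol difference was +0.31 (formula +0.30). The mean intention-to-treat difference was +0.01.

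**The alternative.** Suppose the balloon has effect d in those who receive it, and allocation has no effect in those who do not. The intention-to-treat difference is then d(1 − f), and dividing by (1 − f) recovers d. The per-protocol difference is d + fg. The standard error of the complier estimate is wider by about 1/(1 − f): 1/0.97 = 1.03 at 3% and 1/0.90 = 1.11 at 10%. Estimate and standard error scale together, so its test agrees closely with the intention-to-treat test.

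**The case against.** The strongest objection is that the article commits to very little. Per-protocol is one of two examples, joined by an or, and both depend on the data. The article does not tie it expressly to departures from allocation, and it does not define the set. Both arms have specified debridement and rehabilitation, so a per-protocol set could exclude participants from either arm. Definitions of this kind commonly belong in the statistical analysis plan, which is not shown. This stands to the extent that the missing definition is no fault, and that the exclusion of failed placements is an inference. It does not remove the point. The only analysis named for this purpose is one that does not preserve randomisation, and exclusions for other reasons in both arms would not make up for one that can be seen in only one arm.

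A second objection is that the problem is likely to be small. The Introduction presents deployment as straightforward, and reparability and subscapularis integrity are checked in theatre before randomisation. This also stands, as a reason to expect f to be low.

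A third is that the complier estimate rests on the exclusion restriction, which an abandoned insertion attempt could violate, and that at low non-receipt it adds little to intention to treat. Both are fair. Blinding of participants and assessors makes the restriction more plausible here than in many surgical trials, and close agreement with the intention-to-treat test is a merit in a sensitivity analysis.

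**Conclusion.** The point holds as a minor matter of method choice. As named, per-protocol is open to selection bias of size f × g. At f of 5% or less and g of 6 points or less in either direction, that is at most 0.3 OSS points, with type I error at most about 5.3%. Over the whole assumed range it runs from −0.60 to +1.20 points.

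A reader might infer more than the document supports, in three ways:
- That per-protocol is the planned handling of departures. It is optional and illustrative, and the intention-to-treat primary analysis is untouched.
- That the analysis is certainly biased, and probably towards the balloon. The bias is zero if every balloon is placed or if prognosis is equal, and it reverses if unplaceable shoulders do better. That they do worse is plausible, but nothing in the article says so.
- That the bias amounts to a fifth of the target difference. That needs both 10% non-placement and a 12-point deficit, a full standard deviation.

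The conclusion assumes that the per-protocol set would exclude failed placements and that controls do not receive the balloon.

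**What to change.** In the Statistical analysis plan section, or in the full plan to be agreed with the data monitoring committee, name a complier-average causal effect estimate as the sensitivity analysis for non-receipt of the balloon, in place of per-protocol or ahead of it. Specify:
- randomised arm as the instrument;
- balloon receipt, as recorded on the operative and online forms, as the exposure;
- adjustment for the minimisation factors;
- the exclusion restriction, stated as an assumption, with a comment on abandoned insertions.

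If per-protocol is kept, define its set, label it descriptive, and say that it will not be used to support a conclusion. Apply the same rule to the secondary outcomes.

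The cost is a change of wording and one extra model, with no new data collection. The interval is wider by about 1/(1 − p), where p is the share not receiving the balloon: 3% to 11% for p between 3% and 10%.

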## Health economic evaluation

The economic component will include a standard health policy-relevant economic analysis and an exploration of how early economic data can be used to support decision making through the use of an adaptive design.

A prospective economic evaluation will be integrated into the trial and adhere to the recommendations of the NICE Reference Case.^68^ Mechanisms of missingness of data will be explored and multiple imputation methods will be applied to impute missing data. Imputation sets will be used in bivariate analysis of costs and quality-adjusted life years (QALYs) to generate incremental cost per QALY estimates and confidence regions.^69–72^ It is anticipated that incremental costs and benefits will be captured within the trial and that extrapolated modelling will not be required.

Relatively little research has been conducted on how economic data available at interim time points can inform interim decision making. Currently, methods used are based mainly on net monetary benefit approaches using value of information methods.^73 74^ We will compare various methods using economic data (costs and QALYs) and clinical data to evaluate the practical implications and operating characteristics of stopping a trial early based on cost-effectiveness data alone, efficacy data alone or a combination of cost-effectiveness and efficacy. We will use the trial to evaluate putative analytical methods, as set out within a prospectively written health economic analysis plan and carry out parallel interim analyses, separate from the real trial analyses, exploring how interim decisions might have been influenced. As such health economic decision rules for adaptive designs are less widely understood and used in the literature, the properties of these methods will be developed further for future trials.

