### Outcome measures

#### Primary outcome

The OSS at 12 months. The original study design was based around the Constant score, however the trial management group decided in March 2020, in light of the coronavirus outbreak, to revise this to the OSS. As the Constant score is a face-to-face measure usually taken in hospital clinics, it would have exposed participants to unnecessary risk during the height of the pandemic. The decision was agreed by both the TSCs and DMCs prior to the change.

The OSS has been well validated and used in high-impact randomised trials previously, it correlates well with the Constant score, both are similarly responsive and have comparable effect sizes in rotator cuff pathology.^39–43^ Based on our meta-analysis of outcomes for randomised trials, shoulder scores typically reach a plateau at 12 months after any intervention for a rotator cuff tear.^44^ The 24-month scores do not give sufficient additional value to justify the increase in costs and delay in the trial result that would be required had 24 months been used as the primary outcome.

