#### Secondary outcomes

The OSS at baseline, 3, 6 and 24 months.The Constant Score at baseline, 3, 6 and 12 months. A standardised protocol for the objective component of the score has been developed based on the work of Moeller *et al* with training provided for all sites.^45–47^
Range of pain-free movement of the shoulder at baseline, 3, 6 and 12 months measured using a long-arm goniometer (12 ½”).Strength of shoulder abduction and flexion at baseline, 3, 6 and 12 months measured using a supplied IsoForceControl EVO_2_ dynamometer (Herkules Kunstoff, Switzerland).Western Ontario Rotator Cuff (WORC) index at baseline, 3, 6, 12 and 24 months.^48^
Health utility assessed using 5-level EuroQol 5 dimension score (EQ-5D-5L) at baseline, 3, 6, 12 and 24 months.^49 50^
Healthcare resource collected at 3, 6 and 12 months.Patient Global Impression of Change (PGIC) score, collected at 3, 6, 12 and 24 months. A simple 7-point scale assessing perception of improvement.^51^
Analgesia use (drug and approximate frequency) collected at baseline and 3, 6 and 12 months.MRI Scans (substudy of 56 patients, 6 weeks and 6 months postsurgery): see the ‘MRI substudy’ section.AEs will be collected from site reports as they occur throughout the first 12 months, and from participants in the 3, 6 and 12 months questionnaires.

Patient-reported outcome measures (OSS, WORC, EQ-5D-5L, PGIC) will be collected at 24 months as a secondary outcome, these will be published separately and will not delay publication of the primary 12-month outcome data. A detailed data management plan has been prepared following Warwick SOPs and will be available on request.

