## Statistical analysis

### Power and sample size

The initial sample size calculations were based on the Constant Score. The target difference that was chosen for the Constant Score was 10 units, as has been widely used for other trials, and the SD was taken to be 20, giving a moderate standardised mean difference of 0.5.^17 23 59 60^ Anchor-based studies have estimated the target difference for the OSS as 6 and an SD of 12 has been observed in multiple studies, therefore, a moderate standardised mean difference of 0.5 remains appropriate.^41–43 60^

For a costly invasive procedure of this nature, a smaller standardised mean difference is unlikely to be considered worthwhile. For a power of 90% and a (two-sided) type I error rate of 5% a study with a conventional fixed design (ie, with no possibility of stopping early), assuming an approximate normal distribution for the score data, would require 170 participants.

In order to assess the design characteristics and estimate the required sample size for the planned adaptive design, we undertook a large simulation study (see Parsons *et al*
38). As we expect correlations between time points (based on Karthikeyan *et al)* and effect sizes to be equivalent between the Constant Score and Oxford Scores, these simulations remain valid, despite the change of primary outcome score.^41 60^ The simulations showed that an adaptive design that allowed the possibility of early stopping for efficacy and/or futility, was feasible for the START:REACTS study.

Based on an assumed modest correlation between 3-month, 6-month and 12-month OSSs equal to 0.5, and SD of 12 for both three and 6-month scores, the simulations for the selected adaptive design indicated that 188 participants would be sufficient to detect a 6 point difference in OSS between treatment arms with 90% power, and 5% (two-sided) type I error rate. Allowing for 15% lost to follow-up, while striving to keep this below 10%, gives a maximum study sample size of 221.

The sample size for the MRI substudy is based on the study by Gumina *et al*
55, where the minimum acromiohumeral distance had an SD of 1.72 mm. To observe a minimum important difference of 1.5 mm (larger than the minimum detectable change of 1.3 mm established elsewhere^61^) with an alpha of 0.05 at 80% power, assuming a lost to follow-up at 6 months of 20%, requires 56 participants for the MRI substudy.

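### Resource use is collected only to 12 months while EQ-5D-5L runs to 24, so the collection schedule does not support the expectation that no extrapolation will be needed

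*Protocol article*

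**What the plan says.** All references are to the protocol article.

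- Health economic evaluation: "It is anticipated that incremental costs and benefits will be captured within the trial and that extrapolated modelling will not be required". The section gives no time horizon. It commits to the NICE Reference Case and mentions a health economic analysis plan, which is not shown.
- Secondary outcomes, on costs: "Healthcare resource collected at 3, 6 and 12 months". The secondary clinical objectives give the same three time points for resource use.
- Secondary outcomes, on the second year: "Patient-reported outcome measures (OSS, WORC, EQ-5D-5L, PGIC) will be collected at 24 months as a secondary outcome". This list names its instruments, and resource use is not among them.
- Secondary outcomes and the adverse-event section: adverse events are collected through the first 12 months. The general practitioner is contacted only for participants lost to follow-up at or after 12 months.
- End of trial: follow-up runs to 24 months, with a separate report after the 24-month outcomes.
- Primary outcome, defending the 12-month endpoint: "shoulder scores typically reach a plateau at 12 months after any intervention for a rotator cuff tear".

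**The concern.** Cost-effectiveness is part of the stated aim. The article expects the trial itself to capture all incremental costs and benefits, yet it collects the two sides of the ratio over different periods. Utility is measured for two years and resource use for one.

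The only statement about the course after 12 months is the plateau argument. It serves a clinical endpoint well, since a later reading of a flat score adds little. It does not serve a QALY calculation, because QALYs are an area under a curve: a flat but non-zero gap keeps adding to them. An up-front device cost set against one year of a longer-lasting difference could give a cost per QALY well away from the two-year figure. Any second-year difference in reoperation, injections or physiotherapy would have no scheduled source. An analysis plan can choose a horizon or add a model later, but it cannot recover resource use that was never collected.

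**Working it through.** The article states no device cost, utility difference, discount rate or horizon, so there is no economic figure of its own to reproduce. The check has two parts.

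**1. The expectation against the schedule.** The article could mean either of two horizons.
- 24 months, where the trial ends: EQ-5D-5L is available, but second-year resource use is not. Incremental costs are not captured.
- 12 months: costs and utilities match, but incremental benefits are fully captured only if the utility difference has ended by then. Nothing in the article says that it will have.

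The expectation fails on the first reading and is unsupported on the second.

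**2. Illustrative size.** These inputs are assumptions, not figures from the article. Let d be the utility difference at 12 months. The difference is 0 at baseline, a·d at 3 months, b·d at 6 months and d at 12 months, with straight lines between. Year 2 is discounted at 3.5%.

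First-year QALY difference: Q1 = d × [0.25·a/2 + 0.25·(a+b)/2 + 0.5·(b+1)/2].
- Late ramp (a = 0, b = 0.5): 0 + 0.0625 + 0.375 = 0.4375d
- Middle ramp (a = 0.5, b = 0.75): 0.0625 + 0.15625 + 0.4375 = 0.65625d
- Early ramp (a = b = 1): 0.125 + 0.25 + 0.5 = 0.875d

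Second-year addition: maintained, d/1.035 = 0.966d; linear waning to zero at 24 months, 0.5d/1.035 = 0.483d; no later effect, 0.

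Ratio of the 24-month to the 12-month QALY difference, (Q1 + addition)/Q1:

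| Ramp | No later effect | Linear waning | Maintained |
|---|---|---|---|
| Late | 1.0 | 2.10 | 3.21 |
| Middle | 1.0 | 1.74 | 2.47 |
| Early | 1.0 | 1.55 | 2.10 |

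If the difference is maintained, 12 months captures between 0.4375/1.404 = 31% and 0.875/1.841 = 48% of the 24-month QALY difference.

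With a fixed up-front cost and no later cost difference, cost per QALY falls by the same ratios. For the middle ramp, with an assumed extra cost of 1,000 and d = 0.05:
- 12 months: 1,000/(0.05 × 0.65625) = about 30,500
- 24 months, maintained: 1,000/(0.05 × 1.6224) = about 12,300
- 24 months, waning: 1,000/(0.05 × 1.1393) = about 17,600

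**Sign.** Take d = -0.03, the same cost and ramp, and an assumed value of 20,000 per QALY. Net benefit is 20,000 × (-0.0197) - 1,000 = about -1,390 at 12 months. If d is maintained, it is 20,000 × (-0.0487) - 1,000 = about -1,970 at 24 months. Here the shorter window favours the device.

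**Missing costs.** In the middle, maintained case with d = 0.05, a discounted second-year extra cost of 1,000 × 2.472 - 1,000 = about 1,470 in the balloon arm would bring the 24-month figure back to the 12-month one. A saving in that arm would lower it further. The planned data cannot tell these apart.

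**The case against.** The strongest reply is that the article forecasts and does not forbid. A reader might infer that it rules out extrapolation in advance. The wording is an anticipation, and nothing in it prevents modelling if a difference remains. That stands. So does the point that a condensed article may leave the horizon and scenario analyses to the health economic analysis plan; their absence here is not a fault.

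A reader might also infer that the plateau commits the protocol to a continuing benefit. It does not. The plateau describes typical score levels, not a difference between arms. The device degrades from 3 months and is expected to have deflated by 6, and the MRI substudy asks whether its effect outlasts that. Persistence is an open question in this trial. But an open question is no ground for expecting that extrapolation will be unnecessary.

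Finally, a reader might infer that cost per QALY is biased against the balloon. That needs a positive difference at 12 months, persistence beyond it and no offsetting later costs. With no later difference there is no QALY distortion, and with a harmful effect the distortion runs the other way. The documents fix neither direction nor size.

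None of these replies reaches the collection schedule, which the article states outright.

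**Conclusion.** The point holds as a mismatch in data collection and an expectation that the schedule does not support. It does not hold as a demonstrated bias. If a utility difference remains at 12 months, the 24-month QALY difference could be about 1.6 to 2.1 times the 12-month one under linear waning and about 2.1 to 3.2 times if maintained; with no later effect the factor is 1.0. These ranges rest on the assumed ramps and 3.5% discounting. Carrying them over to cost per QALY also assumes that all the extra cost falls at surgery. Second-year cost differences go unmeasured in every scenario. This is a cheap improvement worth making; it does not affect the primary clinical analysis.

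**What to change.** - Add the resource-use items already in use to the planned 24-month questionnaire, at least shoulder-related admissions, further surgery, injections and physiotherapy.
- Report a 24-month within-trial cost-utility analysis with the separate 24-month report, alongside the 12-month analysis.
- Reword the sentence in Health economic evaluation so that the need for extrapolation is judged on the cost and utility differences at last follow-up, with their confidence intervals. A trigger based only on whether the observed difference is non-zero would almost always fire.

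The cost is a slightly longer questionnaire, one further analysis, and recall over the 12 months from month 12 to month 24, against 6 months for the last interval now collected. Participants already past their 24-month contact when the change is made would lack these items and would have to be handled as missing. No extra visit is needed and the 12-month report is not delayed.
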